**Methods:**

The two-tier care management intervention was guided by a standardized protocol conducted by trained professional care managers (first tier) with the support of trained volunteers (second tier), which lasted for 8-12 weeks. Participants were recruited through collaborating hospitals according to inclusion and exclusion criteria. In order to examine the effectiveness and cost-effectiveness of the two-tier care management intervention, a two-arm randomization multicenter study was designed, including an active comparison group, which was guided by a standardized protocol conducted by trained volunteers. Dyadic participants, including both stroke survivors and their primary caregivers for both groups, were invited to participate in a questionnaire survey using standardized and purposefully developed measures 3 times: before the intervention, immediately after the intervention, and 2 months after the intervention. The primary outcome was family functioning measured by the Family Role Performance Scale and Family Assessment Device-General Functioning Scale. The secondary outcomes included caregiving burden, depressive symptoms, care management strategies, and the incremental cost-effectiveness ratio.

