### Intervention Group

Both groups followed a standardized protocol designed by the research team. The intervention group received a two-tier family-oriented care manager–led intervention consisting of a trained social worker (care manager) and trained volunteers for 2-3 months.

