### Control Group

The control group received a volunteer-led psychosocial education for 2-3 months. Care managers did not provide any direct intervention for the participants in the control group. Stroke survivors were not involved in the control group intervention. All participants completed a questionnaire at 3 different time points (Figure 1). A baseline assessment (T0) was conducted by care managers or volunteers before the start of the intervention. The first follow-up (T1) was conducted by a trained research assistant immediately after completion of the intervention, and the second follow-up (T2) was conducted by a trained research assistant at 2 months after completion of the intervention. Time points were chosen to better evaluate the effectiveness of the intervention and to reduce the attrition rate.

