#### Two-Tier Family-Oriented Care Manager–Led Intervention

The intervention was individualized and tailor-made according to the caregivers’ needs assessment results. Care managers conducted an initial family needs assessment with caregivers to determine the care plan. Baseline assessments and a family genogram were used to assess caregivers’ needs. Measures covered demographic information, stroke knowledge, care management strategies, family conflicts, family functioning, social network, caregiver burden, physical and mental health, and depressive mood. The intervention lasted for 2-3 months with 6-10 weekly sessions at the homes of the caregivers or stroke survivors. Each session lasted for 60-90 minutes. The flexibility in the duration was provided based on the consideration that some participating families were more willing to share and discuss in detail, as evidenced in the pilot experiences. The research team visited each study site every 4 weeks to ensure project progress and held a full team meeting with the 3 NGOs every 12 weeks to share good practices.

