#### Volunteer-Led Psychoeducation (Control Group)

The control group received a standard, non–family-based psychoeducation intervention provided by trained volunteers under the supervision of trained care managers. The intervention lasted for 2 months with 4 weekly sessions held at the homes of the caregivers of stroke survivors in the first month and 2 telephone contacts made in the second month (6 contact points in total). Each session lasted for 60-90 minutes. Care managers did not provide any direct intervention for participants in the control group. Stroke survivors were not involved in the control group intervention. Intervention in the control group consisted of 4 weekly home visits by trained volunteers who provided psychoeducation to caregivers, including (1) medication management and communication with health care professionals, (2) healthy lifestyle, (3) stroke care skills, and (4) stroke rehabilitation knowledge. Finally, 2 telephone contacts were made by trained volunteers to educate caregivers on (1) navigating community resources, and (2) preventing recurrent stroke.

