#### Service Utilization Record

The service utilization of medical and social care services by stroke survivors was obtained. Medical care services include inpatient hospital admission, specialist outpatient, accident and emergency service, and hospital rehabilitation service. Social care services include home care service, daycare service, community rehabilitation service, and residential care service (admission after study intake). The clinical profile and service use data of stroke survivors and the electronic medical records from the Hospital Authority Clinical Management System of Hong Kong will be retrieved regularly until 6 months after the completion of the second follow-up assessment.

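### T1, T2 and the end of record retrieval are timed from completion of each family's intervention, and the control duration is contradictory, so the intervention arm may be assessed later and observed longer by up to one month

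*Protocol article*

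**What the plan says.** All places are in the protocol article.

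- **Anchor of the questionnaires** (Control Group): "The first follow-up (T1) was conducted by a trained research assistant immediately after completion of the intervention". The same section places T2 at 2 months after completion and T0 before the intervention starts.
- **End of the records** (Service Utilization Record): clinical and service-use data "will be retrieved regularly until 6 months after the completion of the second follow-up assessment". No opening date for the window is given.
- **Intervention-arm duration:** "trained social worker (care manager) and trained volunteers for 2-3 months" (Intervention Group); "The intervention lasted for 2-3 months with 6-10 weekly sessions" (Two-Tier Family-Oriented Care Manager–Led Intervention). The abstract puts it at 8-12 weeks. Care managers set the intensity for each family after the needs assessment.
- **Control-arm duration, summary:** "The control group received a volunteer-led psychosocial education for 2-3 months" (Control Group).
- **Control-arm duration, detail:** "The intervention lasted for 2 months with 4 weekly sessions" (Volunteer-Led Psychoeducation). The visits fall in the first month and two telephone contacts in the second, which makes a closed schedule of 6 contacts.
- **Analysis** (Statistical Analysis): an analysis of variance or general linear model compares change between the arms over T0, T1 and T2, treated as common occasions.

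**The concern.** A randomised comparison is cleanest when both arms are measured at the same time after randomisation. Here the clock for T1, T2 and the record cut-off starts when a family finishes its programme. Programme length is a post-randomisation quantity, and only the intervention arm is described as individualised. If its programme can also last longer, two things follow.

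- At T1 and T2, intervention families would have had more time since the start. Caregivers and families may adapt or wear down over that time whatever the treatment, and the planned model would attribute the difference to the arm.
- In the hospital and social-care records, intervention families would have longer to accumulate admissions and service use. That would work against the intervention in any comparison of counts or cumulative risk, and in the cost-effectiveness ratio if service use is costed. The article's cost section lists only staff, travel and programme materials.

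**Working it through.** The article gives no figure for elapsed time by arm, so there is no stated result to reproduce. The check builds the times from the stated durations.

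**Inputs**
- D = programme length: 2 months in control (Volunteer-Led Psychoeducation); 2 to 3 months in the intervention arm (Intervention Group and Two-Tier sections).
- T2 lag = 2 months after completion; record lag = 6 months after T2.
- Admission risk: 30% in 6 months, the control-arm figure in Sample Size Calculation, and 15% for the intervention arm.
- Assumptions: times are counted from the start of the intervention; any wait between randomisation and start is equal in the two arms; the record window opens at the start of the intervention.

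**Step 1: timing.** T1 = D; T2 = D + 2; end of records = D + 2 + 6.

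| | Control, D = 2 | Intervention, D = 2 to 3 | Longer by at most |
|---|---|---|---|
| T1 (months) | 2 | 2 to 3 | 3/2 = 1.50, so 50% |
| T2 (months) | 4 | 4 to 5 | 5/4 = 1.25, so 25% |
| End of records (months) | 10 | 10 to 11 | 11/10 = 1.10, so 10% |

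The gap is 0 to 1 month in every row.

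**Step 2: the other stated control duration.** With D = 2 to 3 months in control as well, the two columns have the same range, and no arm difference follows from the stated durations.

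**Step 3: effect of unequal exposure when treatment does nothing.** Assume a constant hazard:
- hazard = -ln(1 - 0.30)/6 = 0.0594 per month
- 10 months: 1 - exp(-0.594) = 44.8%
- 10.5 months: 46.4%
- 11 months: 1 - exp(-0.654) = 48.0%

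The spurious excess in the intervention arm is 48.0 - 44.8 = 3.2 points if every intervention family takes 3 months, 46.4 - 44.8 = 1.6 points if all take 2.5 months, and 0 if all take 2 months.

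**Step 4: effect under the article's own hypothesis (15% against 30% in 6 months).** The intervention-arm hazard is -ln(0.85)/6 = 0.0271 per month, giving 23.7% at 10 months and 25.8% at 11.
- Equal windows of 10 months: 44.8 - 23.7 = 21.1 points.
- Windows of 10 and 11 months: 44.8 - 25.8 = 19.0 points.

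The apparent benefit shrinks by at most about 2.1 points.

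**The case against.** The strongest reply is that the arm difference is not established. The section that sets the assessment schedule also gives control 2-3 months, the same range as the intervention arm, and the objectives describe the whole trial as lasting 8-12 weeks. A reader might infer that control families were certainly assessed earlier. The documents do not support that, because it depends on which of two conflicting sections describes what was done. This part of the reply stands, and the point is therefore conditional.

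Four further replies carry weight.

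- **The gap may be small or reversed.** Taken literally, 6-10 weekly sessions would last about 6-10 weeks against roughly 8 in control, which is 2 weeks shorter to 2 weeks longer. The same sentence says 2-3 months, so the text cannot settle it; only actual dates can. Care managers are said to set intensity, which need not mean calendar length.
- **The record comparison may already be safe.** The article states when retrieval ends, not the window that will be analysed. The only admission window it states is 6 months after discharge, the same in both arms. A reader might infer that this endpoint is distorted too; it is not, if it is analysed on that window.
- **The admission figures are illustrative.** They carry a hypothesised 6-month post-discharge risk forward to 10-11 months. Participants also came from existing service users, with no stated limit on time since stroke, so the true hazard may differ.
- **Extra time need not favour the intervention.** A reader might infer that it inflates the benefit on the scales. The documents give no basis for a direction or a size, and on service use the bias would run the other way.

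None of this removes the completion anchor or the contradiction on control duration.

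**Conclusion.** The point holds in conditional form. The anchor to completion is stated plainly, the two control durations contradict each other, and the planned model treats T1 and T2 as common occasions. If control lasted a fixed 2 months, intervention families can be assessed 0 to 1 month later. Their records can then run 10-11 months against 10, provided the window opens at the start of the intervention.

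For cumulative admission, the spurious excess against the intervention is 0 to 3.2 points, given a constant hazard of 30% per 6 months. The upper end is reached only if every intervention family takes the full 3 months. For the questionnaire outcomes, including the primary family-functioning scales, neither direction nor size can be derived. The issue is worth correcting before analysis but does not undermine the trial.

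**What to change.** 1. Reconcile the Control Group and Volunteer-Led Psychoeducation sections on how long the control programme ran.
2. Compare service use, and any service use that is costed, over one common number of days from randomisation (or T0) in both arms. Fix that number in advance and discard later records. If the 6-months-after-discharge admission endpoint is used, keep it on its own common window.
3. Report the distribution of actual time from randomisation to T1 and to T2 by arm.
4. As a sensitivity analysis only, model the outcomes on actual time. Assessment time arises after randomisation and may depend on arm, so adjusting for it in the main analysis could absorb part of the treatment effect.
5. Data collection ended in March 2020, so visits cannot be rescheduled. In any future use of this design, time T1 and T2 from randomisation identically in both arms.

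The cost is mainly analysis wording. Up to about one month of intervention-arm records goes unused. Steps 3 and 4 need the assessment dates, which the article does not say were kept; it mentions only a log of sessions and their duration.

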**Figure 1 figure1:**
[figure not shown]
CONSORT flow diagram of the randomized controlled trial with 2 groups. HK: Hong Kong.

### Intervention

Stroke caregiver participants in the intervention group received the following interventions.

#### Two-Tier Family-Oriented Care Manager–Led Intervention

The intervention was individualized and tailor-made according to the caregivers’ needs assessment results. Care managers conducted an initial family needs assessment with caregivers to determine the care plan. Baseline assessments and a family genogram were used to assess caregivers’ needs. Measures covered demographic information, stroke knowledge, care management strategies, family conflicts, family functioning, social network, caregiver burden, physical and mental health, and depressive mood. The intervention lasted for 2-3 months with 6-10 weekly sessions at the homes of the caregivers or stroke survivors. Each session lasted for 60-90 minutes. The flexibility in the duration was provided based on the consideration that some participating families were more willing to share and discuss in detail, as evidenced in the pilot experiences. The research team visited each study site every 4 weeks to ensure project progress and held a full team meeting with the 3 NGOs every 12 weeks to share good practices.

The care managers determined the intensity of the intervention after the initial family needs assessment. The weekly sessions selected out of 22 choices are listed in Table 2. The trained care manager provided the first tier of the intervention, consisting of (1) the family needs assessment (session 1), (2) family support and counseling (sessions 2, 3, 4, 5, 6, and 7), (3) psychological support to caregivers (session 12), and (4) care planning and coordination (session 22). Trained volunteers, supervised by the trained care managers, form the second tier of intervention. They mainly provided in-home services, including (1) psychoeducation (sessions 13, 14, 15, 16, and 17), (2) skill-building (sessions 8, 9, 10, and 11), and (3) social support (sessions 18, 19, 20, and 21). Stroke survivors also took part in up to 4 sessions (sessions 18, 19, 20, and 21) if they agreed and were competent to take part in the intervention. However, the participation of the stroke survivors did not affect their caregivers’ involvement in the study and the intervention. Although the intervention was individualized and tailor-made, the research team provided a standardized protocol to guide the trained care managers as well as the trained volunteers in delivering the intervention. Further, the interventionists recorded the sessions conducted as well as the duration of each session in a service log. Because the collaborating NGOs provided social services or rehabilitation services to stroke survivors, rapport building between care managers and stroke families was ensured. All participating stroke families agreed on the intervention and signed consent forms. Further, care managers built a constant feedback mechanism with the participants, which can ensure participant adherence.

**Table 2 table2:** Domains and themes of the intervention sessions.

Domain	Theme	Interventionist	
		Care Manager	Volunteer
Family Needs Assessment	Project orientation, family needs assessment, and goal setting	✔	
Family Support I	Family conference	✔	
Family Support II	Addressing relationship and caregiving issues of spousal caregiver	✔	
Family Support III	Addressing relationship and caregiving issues of adult-child caregiver	✔	
Family Support IV	Rediscovery of family strengths	✔	
Family Support V	Emotion management	✔	
Family Support VI	Empower stroke survivor	✔	
Skill Building I	Caregiver self-care and relaxation		✔
Skill Building II	Mastering care skills		✔
Skill Building III	Communicating with stroke survivor with communication or swallowing problems		✔
Skill Building IV	Communicating with health care professionals		✔
Skill Building V	Stress coping and problem-solving	✔	
Psychoeducation I	Understand poststroke health issues		✔
Psychoeducation II	Medication management		✔
Psychoeducation III	Home safety and emergency handling		✔
Psychoeducation IV	Promoting healthy lifestyle		✔
Psychoeducation V	Navigating community resources		✔
Social Support I	Speech training		✔
Social Support II	Cognitive stimulating activities		✔
Social Support III	In-home rehabilitation exercise		✔
Social Support IV	Family outing	✔	✔
Social Support V	Care plan and coordination	✔	

#### Volunteer-Led Psychoeducation (Control Group)

The control group received a standard, non–family-based psychoeducation intervention provided by trained volunteers under the supervision of trained care managers. The intervention lasted for 2 months with 4 weekly sessions held at the homes of the caregivers of stroke survivors in the first month and 2 telephone contacts made in the second month (6 contact points in total). Each session lasted for 60-90 minutes. Care managers did not provide any direct intervention for participants in the control group. Stroke survivors were not involved in the control group intervention. Intervention in the control group consisted of 4 weekly home visits by trained volunteers who provided psychoeducation to caregivers, including (1) medication management and communication with health care professionals, (2) healthy lifestyle, (3) stroke care skills, and (4) stroke rehabilitation knowledge. Finally, 2 telephone contacts were made by trained volunteers to educate caregivers on (1) navigating community resources, and (2) preventing recurrent stroke.

### Outcomes

#### Primary Outcome Measures

The primary outcome revolves around the family level. The family-level outcome measures to be obtained include the Family Role Performance Scale, Care Management Strategies Scale, FCCS, and Family Assessment Device-General Functioning (FAD-GF) scale. The details of each scale are described below (Table 3).

**Table 3 table3:** Outcome measures.

Outcome measures			Baseline		First follow-up		Second follow-up		Six months after second follow-up

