**Primary outcomes**									
	Family Role Performance Scale	✔		✔		✔			
	Family Assessment Device-General Functioning Scale	✔		✔		✔			

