**Secondary outcomes**									
	Care Management Strategies Scale	✔		✔		✔			
	Family Caregiver Conflict Scale	✔		✔		✔			
	Cantonese short version of Zarit Burden Interview	✔		✔		✔			
	The Patient Health Questionnaire-9 item	✔		✔		✔			
	Caregiving Ambivalence Scale	✔		✔		✔			
	Social care services used by stroke survivors	✔		✔		✔			
	Medical care services used by stroke survivors	✔		✔		✔			
	Clinical profile and service use data of stroke survivors							✔	
	Cost of study participation							✔	

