#### Family Role Performance Scale

The research team developed this scale to measure the frequency and ability of the family member to perform 6 major family roles, that is, advisor, emotional connector, breadwinner, caretaker, decision maker, and caregiver by using the structure developed and validated by Chen et al [19]. This scale contains 2 parts. The first part contains 6 items and asks participants how often they perform the 6 family roles. Each item is answered on a scale ranging from 0 (*never*) to 4 (*very frequently*). The second part contains 6 items and asks participants to rate their performance regarding family roles. Each item is answered on a scale ranging from 0 (*very poor*) to 4 (*very good*). The 2 parts will be scored separately.

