### Statistical Analysis

We will use descriptive statistics to present baseline characteristics and outcome measures, and we will transform any skewed variables and correct their skewness before inferential analysis. To assess normality, we will perform the Shapiro-Wilk test of normality as well as the normal Q-Q Plot, while we will use the Wilcoxon signed-rank test for the nonparametric test. We will also perform the chi-square or independent two-tailed *t* tests to examine the differences in the baseline characteristics between the intervention and control groups. For the primary and secondary outcomes, we will perform a multi-factor analysis of variance or general linear model to compare the differential changes in each outcome across the 3 assessment time points, that is, T0, T1, and T2 between the 2 treatment groups. This model can account for repeated measures data that are intercorrelated and that produce unbiased estimates even in the presence of the missing data, provided that the data are missing at random. Multivariate regression will be used to compare the differences in the outcomes between the 2 treatment groups and will control for the effect of potential covariates such as depressive symptoms and caregiver burden. Recruitment rate, attrition rate, and missing data will also be examined and reported. All outcome measures will be analyzed based on intention-to-treat principles. Every participant who is randomized according to the randomized treatment assignment will be included. This method of analysis preserves the prognostic balance afforded by randomization [25]. The cost of study participation, including staff cost, travel expenses, and program materials, will be expressed in Hong Kong dollars. All the statistical analyses will be performed using SPSS Statistics. All statistical tests will be two-sided with the level of significance set at .05.

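### The list of primary outcomes is two scales in the abstract and Table 3 but four in the outcomes text, leaving three or at least five primary scores, each tested at the full .05

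*Protocol article*

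**What the plan says.** The protocol article defines the primary outcome in three places.

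- **Abstract, Methods:** "The primary outcome was family functioning measured by the Family Role Performance Scale and Family Assessment Device-General Functioning Scale". The next sentence puts care management on the other side of the line: "The secondary outcomes included caregiving burden, depressive symptoms, care management strategies, and the incremental cost-effectiveness ratio".
- **Outcomes, Primary Outcome Measures:** the text ties the primary outcome to the family level and says the family-level "outcome measures to be obtained include the Family Role Performance Scale, Care Management Strategies Scale, FCCS, and Family Assessment Device-General Functioning" scale. That is four scales.
- **Table 3:** the primary block has two rows, "Family Role Performance Scale" and the FAD-GF. The secondary block includes "Care Management Strategies Scale" and "Family Caregiver Conflict Scale".

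The text under Secondary Outcome Measures describes that tier as mainly personal-level. It names the burden, depression and ambivalence scales, but neither Care Management Strategies nor the FCCS.

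On scoring, the Family Role Performance Scale has a frequency part and a performance part: "The 2 parts will be scored separately". No total and no lead score is given. On error control, Statistical Analysis says: "All statistical tests will be two-sided with the level of significance set at .05".

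**The concern.** Two scales, Care Management Strategies and the FCCS, are primary in one place and secondary in another. A positive result on either could be reported as primary with one passage cited, and a negative result could be demoted with another.

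Even on the shorter list, naming two scales does not mean two tests, because one scale gives two scores and neither leads. With each score tested at the full .05, the article does not say what a mixed result means, for example FAD-GF significant and both role scores not. Whether the trial-level false-positive rate stays near 5% or rises well above it depends on a success rule that the article does not state.

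**Working it through.** **Step 1. Count the primary scores.**

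| Source | Scores | Count |
|---|---|---|
| Abstract and Table 3 | role frequency, role performance, FAD-GF | 3 |
| Text under Primary Outcome Measures | those three, plus Care Management composite and FCCS | 5 |

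Five is a minimum for the long list. The Care Management Strategies Scale is also scored in two parts before its composite is formed, and the FCCS has four subscales.

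**Step 2. False-positive rate if any one significant score counts as success.** The per-test level is .05 two-sided (Statistical Analysis). With no true effect and k independent tests, the rate is 1 − 0.95^k.

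- k = 3: 1 − 0.95³ = 0.143
- k = 5: 1 − 0.95⁵ = 0.226

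The scales come from the same respondent and are probably correlated, but the article gives no correlations. The values below are therefore assumptions. They come from simulating k equally correlated two-sided z-tests with 400,000 draws.

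| k | independent | 0.3 | 0.5 | 0.7 | 0.8 |
|---|---|---|---|---|---|
| 3 | 14.3% | 13.6% | 12.5% | 10.9% | 9.9% |
| 5 | 22.6% | 21.0% | 18.3% | 14.8% | 12.7% |

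Even at a correlation of 0.8, three scores roughly double the nominal 5%.

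**Step 3. False-positive rate if all primary scores must succeed.** A false claim then requires every score to be significant, so the rate cannot exceed that of a single test. With no true effect on any score it is below 5%; for three independent scores it is 0.05³ = 0.000125.

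**Step 4. Power cost of controlling the error over three scores.** Holm's strictest step uses .05/3 = .0167. For a simple two-group comparison with n per arm and 80% power, the detectable standardised difference is d = (z₁₋α/₂ + z₀.₈₀) × √(2/n), with z₀.₈₀ = 0.842, z = 1.960 at .05 and z = 2.394 at .0167. The article allows two plausible values of n, both using its planned 25% attrition and an even split:

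- 264 enrolled: 264 × 0.75 / 2 = 99 per arm. √(2/99) = 0.142. d = 2.802 × 0.142 = 0.40 at .05, and 3.236 × 0.142 = 0.46 at .0167.
- 200 with baseline questionnaires: 200 × 0.75 / 2 = 75 per arm. √(2/75) = 0.163. d = 2.802 × 0.163 = 0.46 at .05, and 3.236 × 0.163 = 0.53 at .0167.

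These are guides only. A group-by-time test over three assessments has a different power function, which depends on within-person correlations that the article does not give.

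**The case against.** The case on the other side has real weight.

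- **The abstract and Table 3 agree.** The outcomes text is the outlier, and it refers the reader to Table 3. It can be read as listing all family-level measures, not only the primary ones, and the word mainly in the secondary-outcome text leaves room for family-level secondaries. A reader might infer that the sponsor is free to pick any of four scales after seeing the data. The published two-scale list limits that, and the five-score figures apply only if the outcomes text overrides the other two places. The conflict still stands, because the four scales sit under a heading that calls them primary.
- **The inflation depends on a success rule.** A reader might infer that inflation is a fact of this design. It follows only if any one significant score counts, and the article does not say so. An all-must-succeed rule is neither written nor excluded.
- **T1 and T2 are not planned as separate tests.** A reader might double the count to 6 or 10 tests and arrive at 26% to 40% (1 − 0.95⁶ = 0.265; 1 − 0.95¹⁰ = 0.401). Statistical Analysis instead describes one comparison of change across the three assessments for each outcome. Repeated scores on one scale are also correlated, so those figures would be upper bounds on an analysis that is not described.
- **The covariate regression need not be a second primary analysis.** The analysis of variance or general linear model is assigned expressly to the primary and secondary outcomes. The regression can be read as supportive, although the wording is loose.
- **A separate analysis plan may set a hierarchy.** Its absence from the article is not a fault. Such a plan would still have to choose between two printed primary lists, and any adjustment would have to be reconciled with the flat .05 printed here.

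**Conclusion.** The article contradicts itself on which scales are primary, and this needs correcting. On the abstract and Table 3 there are three primary scores; on the outcomes text there are at least five. Each is tested at two-sided .05.

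If any one significant score counts as success, the false-positive rate for the primary claim is about 10-14% with three scores and about 13-23% with five. The ends of these ranges are an assumed correlation of 0.8 and independence. If all scores must succeed, the rate is below 5%. The label conflict and the score counts come directly from the text; the error rates rest on the assumed success rule and correlations.

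**What to change.** 1. Make the text under Primary Outcome Measures agree with the abstract and Table 3 by moving Care Management Strategies and the FCCS to the secondary outcomes.
2. State that there are three primary scores: FAD-GF, role frequency and role performance. Test each by the group-by-time comparison of the repeated-measures model already planned, with Holm control at a family-wise two-sided .05, and base any primary claim on the Holm-adjusted p-values.
3. Label the covariate regression as supportive.
4. Date the change. The article reports data collection complete in March 2020, with results still to be published. The rule should be shown to predate any unblinded comparison; if it does not, the report should say it was set afterwards.

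The cost is wording and a small loss of power. For a simple two-group comparison, the detectable d rises from about 0.40 to at most 0.46 at 99 per arm, or from about 0.46 to at most 0.53 at 75 per arm. These are upper limits because Holm relaxes the level after each rejection.
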